### Aim and objectives

This 24-month research study initiative aims to engage a private provider network in select union councils of Islamabad Capital Authority (ICT) of Pakistan to improve access, uptake, and satisfaction and reduce OOP expenditure on quality OPD services at the primary health care level, including family planning and sexual and reproductive health services.

The specific objectives of this intervention are:

Examine and document the determinants of outpatient services access and uptake.Measure the changes in OOP expenditures, treatment outcomes, user satisfaction and quality of care.Study and document health insurance outcomes using the capitation model intervention for modified outpatient EPHS services.Generate evidence for the scale-up and delivery of integrated services as OPD services through SSP.*Users, providers, and policymakers’ perspectives will be examined and documented.

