#### The theory of change

The assumption is that access to primary health care services will increase by deploying private general practitioners (GPs) in select areas where public sector-owned primary-level facilities are unavailable. Three components of the theory of change are (a) the Demand Side, (b) the Supply Side, and (c) Evidence generation.

The supply-side and demand-side components will be combined while health financing using capitation for PHC may create demand, thereby increasing the utilization of PHC services for the poorest of the poor outpatients. Evidence will be generated by documenting the extent to which the needs of the beneficiaries are met with quality, equitable, sustainable PHC service and if this has redefined health-seeking behavior at the community level. Evidence will also provide an understanding of the suitability of the intervention with possible recommendations for health financing and its scalability. Each component has a defined set of activities/interventions to achieve the desired output, immediate, intermediate, and ultimate outcomes (Figure 1). From an individual and household perspective, the ultimate outcome is designed to reduce out-of-pocket expenditure while increasing immunization status, contraceptive use, financial protection, and treatment effects among the enrolled beneficiaries (refer to Figure 1). While at the health facility level, this project emphasizes the delivery of quality health service by enhancing the clinical and counseling skills of health service providers, resulting in increased client flow and revenue for the self-suitability of the service delivery channels.

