#### The logical framework

The proposed framework will describe the process of evaluating the quantitative outcomes of health care costs on families covered by health insurance schemes who receive OPD services (intervention arm) as compared to those covered under SSP but do not receive OPD services (control arm). Figure 2 summarizes inputs, processes, or outputs leading to intended outcomes.

The logical flow of the theory of change emphasizes the intermediate and immediate outcomes of improving the attitude toward health-seeking behavior of the beneficiaries based on the Information, Education and Communication (IEC) material and awareness about health services. While the capacity building of the service providers will increase client-centric communication, clinical monitoring, client exit interview surveys, and routine data gathering, its usage will ensure quality health service delivery and improvement. This intervention has been designed to address the financial barrier that restricts access to primary health care services. Hence, this project is expected to improve access and uptake, reduce out-of-pocket expenditure for quality outpatient health services at the PHC level, and produce evidence for recommendations and their scalability.

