#### Capitation-based provider payment mechanism (PPM)

For this research study, a proposed capitation payment mechanism will be implemented as a test case within the country’s existing health systems due to the desire to contain the cost of care provision. Literature indicates that capitation is expected to promote efficient use of resources by controlling prices and volumes of services provided. Capitations have been used both as stand-alone or blended capitations in large parts of Europe, Thailand, South Korea etc. (44) which not only help in managing cost and serve as a critical source of income for the providers (45) but are also associated with increased adherence to policies and general guidelines on the part of providers (46). In this research study, recruited providers will receive a fixed payment to provide a pre-defined benefit package of EPHS to each enrolled family allocated to their facility over a fixed period of 12 months. The implementing partner (Marie Stopes, Pakistan) will disburse the provider capitation fee on a four (4) quarterly payment cycle.

To determine the best capitation mechanism, this study proposes to test and evaluate a quarterly capitation fee totaling PKR 2,900 (USD 17.55) (47) paid to service providers per family per year. The amount for capitation was decided based on essential services selected for the implementation of this research study. The essential services were derived from Pakistan’s UHC benefit package at the PHC level. Payment of capitation fees will be independent of service provision and will not depend upon all or a fraction of enrolled families utilizing the services.

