#### Study population and sample size

The target population will be divided into (a) demand-side and (b) supply-side.

*Demand Side:* The total sample size for this study is 1726 beneficiary families (Baseline and end-line: control and intervention). This has been calculated by assuming the overall prevalence of health outcomes to be 50% (conventional) at baseline and an anticipated 10-percentage point change because of the intervention; with 80% power and 0.05 significance level, the total estimated sample was 388 for each study arm. The estimated sample was adjusted for a design effect 2 to account for facility-level clustering and 10% missing data / non-response. Hence an overall sample size of 863 families in the intervention- and 863 families in the control- group will be required to test the study objectives. Families in each study arm will be selected randomly from the available list of SSP beneficiary families from four peri-urban Union Councils of Islamabad Capital Territory (ICT). The intervention group (*N* = 863) will receive modified EPHS interventions as OPD services, while the Control group (*N* = 863) will not receive OPD services. Enrolled families in the intervention group will be informed about the project, and regular follow-up of SSP outpatient services accessed will be undertaken.

*Supply Side:* GPs who are members of Marie Stopes Pakistan’s primary healthcare franchise network will be selected based on their service provision status within the UCs identified for research study implementation. Individual and facility assessments will be done to ascertain the capacity to provide quality OP services to clients. A training curriculum will be jointly developed by the MoNHSRC, SSP, MSS, and WHO and will be used to train the selected GPs on the modified EPHS services. Periodic quality assurance visits and a centralized data-collection management information system will be implemented.

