### Quantitative household surveys

Before initiating the intervention, a household-based baseline survey is proposed that will cover not only the study population but also a subset of the general population from the same catchment who do not have the provision of any public or private sector health insurance. Findings will explore and explain health-related expenses and payment mechanisms if practiced or that exist other than the fee for service paid through OOP by clients in the study catchment area. The baseline survey will assess the prevalence of study indicators, document socio-economic and demographic information, out-of-pocket health expenditure, and document KAP regarding existing inpatient coverage and access and uptake of health services. A household-based endline survey at the end of 12 months of the intervention will help assess study outcomes – the impact of the outpatient services model on knowledge, attitude, and practice regarding health insurance, access, and uptake of outpatient services at the PHC level, user satisfaction, treatment outcomes, OOP health expenditure and financial protection.

Study participants for baseline and end-line assessment across the intervention and comparison arm will be selected randomly from the list frame of the SSP. Using quantitative and qualitative techniques, data collection methods will include a population-based household survey, providers’ assessment, and specific qualitative inquiry during the intervention, routine services, client satisfaction, and monitoring (clinical quality assessment) data will be done similarly to a previous study using the same design (50).

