#### Data analysis

The quantitative data analysis will focus on the combined effect of the complete package of interventions and the outcome(s) rather than exploring each component. Quantitative data will be analyzed through SPSS Software using descriptive and inferential statistics. The main outcome variables will be increased access, uptake, satisfaction, contraceptive prevalence, and reduction in OOP expenditure. Difference-in-differences (DiD) estimation will compare key outcome variables between the intervention and control group pre- and post-intervention (51). It will also measure the intervention effect on any subgroups in the intervention/control groups by comparing key outcome variables between beneficiaries in the intervention and control groups.

For the qualitative data, content and thematic analysis will be done in Nvivo Software version 11. Codes will be developed after reading the transcripts without losing the context. For qualitative analyses, transcripts will be read several times to understand the respondents’ in-depth experiences and views. ‘Meaning units’ that mirror statements will be identified as per the topic guide by highlighting phrases in the transcripts, which will be ‘condensed’, and after that ‘, codes’ will be identified from the ‘condensed meaning units’ without losing the context. Finally, the research team will review the codes independently and group similar codes into sub-categories and categories. From the categories, themes and sub-themes will be identified after systematically analyzing the commonalities, variations, and disagreements. We will further analyse data with a focus on the description and interpretation of message meaning and concepts to validate the study’s findings. Quantitative and qualitative data will be triangulated to provide comprehensive information about the impact of the research intervention. Figure 3 describes the components of the data synthesis plan envisaged for the project.

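### A difference-in-differences on satisfaction among users only would mix any real effect with a change in who uses care, and the stated 80% power does not cover such an outcome

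*Protocol article*

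**What the plan says.** The Data analysis section of the protocol article names the main outcomes: "The main outcome variables will be increased access, uptake, satisfaction, contraceptive prevalence, and reduction in OOP expenditure". It then gives the method: "Difference-in-differences (DiD) estimation will compare key outcome variables between the intervention and control group pre- and post-intervention". Uptake and satisfaction therefore stand side by side as main outcomes under one analysis.

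Two other sections show what kind of satisfaction is meant. The second objective under Aim and objectives is "Measure the changes in OOP expenditures, treatment outcomes, user satisfaction and quality of care". Quantitative household surveys lists among the endline outcomes "user satisfaction, treatment outcomes, OOP health expenditure and financial protection". Treatment outcomes appear in both places but not in the main-outcome sentence.

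The article also expects the intervention to change use. The theory of change says that "health financing using capitation for PHC may create demand, thereby increasing the utilization of PHC services", and the logical framework says that "this project is expected to improve access and uptake, reduce out-of-pocket expenditure for quality outpatient health services at the PHC level".

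The sample size (Study population and sample size) is a single two-proportion calculation, made by "assuming the overall prevalence of health outcomes to be 50% (conventional) at baseline and an anticipated 10-percentage point change because of the intervention". It gives 388 per arm, raised to 863 by a design effect of 2 and 10% missing data or non-response. The article gives no share of study families expected to use outpatient care.

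**The concern.** A family that made no outpatient visit has no experience of care to rate. The most natural analysis of user satisfaction takes the families with a score, that is, the users. Being a user at endline is something the intervention is designed to alter, so this analysis conditions on a post-intervention variable.

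DiD removes fixed differences between the arms and changes common to both. It does not remove a change in the mix of users that the intervention causes in one arm. Families drawn in by free care may well differ in satisfaction from families who were already paying for it, and only the intervention arm gains them for this reason. Random selection of families from the beneficiary list does not help, because the shift arises after selection.

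The results are meant to inform scale-up. A gain or loss in user satisfaction could be read as an effect on quality when it partly or wholly reflects who was asked. Treatment outcomes raise the same difficulty.

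**Working it through.** **1. The plan's own figure.** Inputs from Study population and sample size: 50% against 60%, 80% power, 0.05 significance level (two-sided taken; sidedness is not stated).

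n = [1.960·√(2·0.55·0.45) + 0.842·√(0.5·0.5 + 0.6·0.4)]² / 0.10² = (1.379 + 0.589)² / 0.01 ≈ 387.3, so 388 per arm.

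388 × 2 / 0.9 = 862.2, so 863 per arm. Both figures reproduce. Working back, 863 × 0.9 / 2 = 388.35 effective families per arm, with 80.1% power. This holds only if every responding family supplies the outcome.

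**2. Shift in the user-only DiD when no family changes.** Let b be the share already using care, i the extra share drawn in by the intervention, and s_b and s_i their satisfaction. Control-arm use and satisfaction stay constant. Then

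spurious DiD = (b·s_b + i·s_i)/(b + i) − s_b = i·(s_i − s_b)/(b + i).

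All of these rates are assumptions. With s_b = 70% and s_i = 50% or 90%:

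| Use, before to after | Spurious DiD |
|---|---|
| 30% to 40% | 10 × (±20)/40 = ±5.0 points |
| 50% to 60% | 10 × (±20)/60 = ±3.3 points |
| 50% to 70% | 20 × (±20)/70 = ±5.7 points |
| 80% to 90% | 10 × (±20)/90 = ±2.2 points |

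The sign follows whether new users are more or less satisfied than existing ones. The shift is zero only if they are equally satisfied or if use does not change.

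**3. Power if only users are scored.** The first calculation is an endline comparison of 50% with 60%, the kind of test the plan is sized on. The effective number is 863 × 0.9 × u / design effect, where u is the assumed share of users. The design effect is either held at 2 or reduced to about 1 + u, because fewer scored families per facility means less clustering at a fixed intraclass correlation.

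| Use, control / intervention | Design effect 2 | Design effect about 1 + u |
|---|---|---|
| 100% / 100% | 80% | 80% |
| 90% / 90% | 76% | 78% |
| 70% / 80% | 68% | 74% |
| 50% / 60% | 54% | 65% |
| 30% / 40% | about 37% | 52% |

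**4. The same for a DiD.** Here the four cell variances are summed for a 10-point effect, with the design effect held at 2.

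| Families scored | Independent surveys | Within-family correlation 0.5 (assumed) |
|---|---|---|
| All | 51% | 80% |
| 90% users | 47% | 76% |
| 50% users | 29% | 51% |

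The drop down each column is the cost of restricting to users: about 4 points at 90% use, and 22 to 29 points at 50%. The 51% in the first row applies to every outcome and is a separate matter.

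**The case against.** The strongest reply is that the analysis at fault is nowhere written down. The article does not restrict the DiD to users, and a condensed article may leave an outcome's denominator to a full protocol or analysis plan. This is right as far as it goes: a reader might infer that a user-only DiD is planned, and the text does not establish that. But the article itself makes satisfaction a main DiD outcome, calls it user satisfaction, places it beside uptake, and sizes the study as if every family were scored. That combination is on the page, and its default reading leads to the biased comparison.

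A reader might also infer that power is far below 80%. The documents do not support this. They give no use rate for the study families. The 50% in the sample size is labelled conventional and refers to health outcomes, not to use. The unit is a whole family, and if most families make at least one visit in the recall period the loss is small. Nor is the capitation rule evidence of low use: the statement that payment "will not depend upon all or a fraction of enrolled families utilizing the services" says how providers are paid and does not forecast how many families will come.

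A third objection concerns the remedy. An all-family outcome of having used care and been satisfied rises mechanically with uptake. With the 50% to 60% example it goes from 0.50 × 70% = 35% to 35% + 0.10 × 50% = 40%, or to 35% + 0.10 × 90% = 44%, with existing users unchanged. It also scores a family that needed no care like a dissatisfied one. This stands, and the measure should support the user-only figure, not replace it as the main outcome.

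Finally, treatment outcomes are an objective and an endline outcome but are not named among the main outcomes, so the point applies to them with less weight.

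**Conclusion.** The concern holds in a limited form. Because uptake is expected to rise through the intervention, a DiD on satisfaction among users does not isolate an effect on satisfaction. Under the assumed rates the distortion is about 3.3 points either way at 50% to 60% use, and roughly 2 to 6 points over the range shown, against a 10-point design effect. Its direction cannot be known in advance.

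The stated 80% power belongs to outcomes scored in all families. For a user-only outcome it is lower by an amount the documents do not allow one to fix. On the plan's own type of test it is about 76% to 78% at 90% use, and about 54% to 65% at 50%/60% use, depending on how the design effect is treated. The existence of a shortfall follows from the text; its size rests on the use rate, which is an assumption.

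**What to change.** In Data analysis:

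- Report satisfaction among users, and treatment outcomes among users, as descriptive results. Show them beside the share of families using outpatient care by arm and wave, and do not present the user-only DiD as the intervention effect.
- Add a supporting outcome defined over all enrolled families: the family used outpatient care in the recall period and was satisfied with it. State that it partly reflects uptake.

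In Study population and sample size, state that the 80% power applies to outcomes scored in all families.

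The cost is analysis wording, with no change to the sample. One check is needed: user satisfaction is named explicitly only for the endline survey, so the baseline questionnaire should be confirmed to record use and satisfaction too. The price is that satisfaction among users no longer carries a causal claim.

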**Figure 3 fig3:**
[figure not shown]
The evidence synthesis plan.

### Ethics and dissemination

The study received formal ethical approval from the Research and Development Solutions, Pakistan-Institutional Review Board (IRB00010843). Preserving the highest standards of ethics in research and practice is critical. Hence, actions will be taken to ensure the highest standards of ethics for the quality of collected data. Informed written consent will be taken from all research participants in their native language. No personal identifying information will link recorded data to a specific individual. Steps will also be taken to ensure privacy (both auditory and visual) during interviews. Unique IDs will be issued to each participant based on the home address and allocated PHC facility so that the names of any participant might not be disclosed. The same unique identifier will identify all data forms, reports, and other records to maintain participant confidentiality. All the data documents will be kept in the custody of authorized personnel in locked cabinets and shared only with authorized personnel. Participants will also be notified of their rights to withdraw from the study at any time if they so choose, as well as their right to skip any questions during baseline/endline assessment if they do not feel comfortable answering without facing any penalties. A core group will be represented by the Ministry of Health Government of Pakistan, MSS-P, SSP, and WHO which will be responsible for programmatic decision-making. At the initial design phase, this core group will finalize and approve the modified EPHS to be used in the research intervention, jointly develop a training curriculum for the GPs and finalize the amount for capitation based on the modified EPHS for this research study. Findings emerging from this research study will be disseminated through peer-reviewed journal publications, presentations at relevant conferences, and shared with key stakeholders engaged in this project, including government officials and the World Health Organization.

## Discussion

People living in LMIC, including in Pakistan, often do not benefit from primary health care programs for early detection and treatment of people with risk factors for multiple diseases; the poorest are the most affected. Around 50% of the population in Pakistan does not have access to primary healthcare services, and a similar proportion of the population does not have health insurance, which seems to contribute to poverty due to catastrophic health spending and high out-of-pocket expenditure. Evidence suggests that emphasis should be placed on primary health care to achieve universal health coverage. The private sector can be a major provider of essential services where the public sector has capacity (human resources/coverage/finances) constraints. Therefore, the proposed research study is expected to address the gap in the SSP program by engaging private sector service providers for outpatient services at the primary healthcare level to reduce the out-of-pocket expenditure of the already enrolled beneficiaries, thus improving universal health coverage. Finally, it will help to develop a blueprint referral system to reduce unnecessary hospital admissions and improve timely access to healthcare. Expanding the reach of basic primary healthcare services is crucial to improving health and providing ready access to basic healthcare services, including sexual reproductive health services under primary care, can reduce hospitalizations, morbidity, and mortality, increase life expectancy, and deliver better overall health.

